**Fig. 1 Fig1:**
[figure not shown]
Example colorectal cancer risk report and screening recommendations for a participant at average risk in the SCRIPT study

**Fig. 2 Fig2:**
[figure not shown]
Example colorectal cancer risk report and screening recommendations for a participant at moderate risk in the SCRIPT study

### Criteria for discontinuing or modifying allocated interventions {11b}

Participants can withdraw from the study at any time without giving a reason, as stated to them prior to informed consent. If this occurs prior to provision of CRC risk results, participants will not receive the full intervention. Participants will be given the choice as to whether their withdrawal will only be from further contact from the trial team or withdrawal of all their unanalysed data.

### Strategies to improve adherence to interventions {11c}

For those who do not attend their scheduled risk result appointment, three attempts will be made to reschedule. After three unsuccessful contacts or three non-attendances at their result appointment, they will be sent their risk results in the post and a copy uploaded to their GP record.

During the initial presentation of the study procedures and purpose with GPs prior to their consent, they will be encouraged to discuss the risk information provided to their patients in the trial and order screening according to their clinical judgement. To reduce the risk of contamination in the control arm, we will encourage each GP to continue their normal practice with patients who do not have a CRC risk report. We will assess potential contamination during the trial by what proportion of participants in the control arm have GP-ordered iFOBTs within 4 weeks of consent.

### Relevant concomitant care permitted or prohibited during the trial {11d}

No alteration to usual care is required during the trial, and therefore, there is no concomitant care that is prohibited.

### Provisions for post-trial care {30}

There are no anticipated harms associated with the intervention in the study. All participants are recommended CRC screening at least as much as what is recommended in the NHMRC guidelines. Additionally, GPs in the study are informed that they should use their clinical judgement along with the personalised CRC screening recommendations; clinical responsibility remains with each participant’s GP. Previous studies returned genomic risk results for cancer have not found a substantial risk of anxiety or psychological harm from knowledge of future risk [44]. Therefore, there are no provisions for post-trial care.

### Outcomes {12}

#### Primary outcome

The primary outcome is the difference between the two arms in the proportion of participants who have had risk-appropriate CRC screening at 12 months’ follow-up. The appropriate screening test in the intervention arm will be determined by the screening recommended according to their absolute 10-year risk of CRC derived from the PRS and family history. For those in the control arm, the appropriate screening test is determined by family history according to the NHMRC guidelines [5].

Risk-appropriateness of CRC screening was chosen as the primary outcome as previous cost-effectiveness studies have shown that CRC population screening targeted using a PRS would be cost-effective if the behavioural effect of returning the risk estimate increased screening by 5% [45]. Additionally, a study modelling the impact of various participation levels in the Australian NBCSP showed that increasing participation from 40 to 60% would result in 24,800 deaths prevented [3].

#### Secondary outcomes

Difference between the SCRIPT intervention arm and standard cancer prevention information arm for the following secondary outcomes:Perceived personal risk of CRC, using mean absolute risk estimates and proportions estimating themselves as average, higher than average and lower than average at 1, 6 and 12 months, will be measured using existing validated items [46]Mean cancer-specific anxiety at 1, 6 and 12 months on the Cancer Worry Scale [47]Mean scores of predictors of CRC screening behaviour (salience and coherence, response efficacy, cancer worries, social influence, self-efficacy) at 1, 6 and 12 months taken from the Preventative Health Model [48]Proportions with CRC screening intentions at 1 and 6 months based on the Theory of Planned Behaviour [49]Mean costs of delivering the SCRIPT intervention (pre- and post-test consultations, buccal kits and SNP test) and the control consultation, as well as health service utilisation and direct health care costs at 12 monthsRisk-appropriate screening behaviour after 5 years

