#### Secondary outcomes

Data for secondary outcomes will be collected primarily from participants’ questionnaires at 1, 6 and 12 months post-intervention delivery.Participants will be asked to state their CRC risk perception numerically, on a scale from 0 to 100, and comparatively to an ‘average’ person, from 1 — much lower — to 7 — much higher [46].The Cancer Worry Scale [47] is a validated, 6-item scale measuring anxiety about the risk of CRC. Each item is rated on a 1–4 scale (not at all or rarely to almost all the time) and then summed for a total.The Preventative Health Model [48] is an 18-item, validated scale, answered on a five-point Likert scale from strongly disagree to strongly agree. It measures known predictors of CRC screening behaviour in five subscales: salience and coherence (4 items), response efficacy (2 items), cancer worries (2 items), social influence (4 items) and self-efficacy (6 items). Each subscale is summed for a total.CRC screening intentions to undertake screening or discuss screening with their GP will be measured with a five-point Likert scale from strongly disagree to strongly agree.The cost of the SCRIPT intervention, health service utilisation and health care costs will be calculated based on the assessment of GP consultations, colonoscopy services, iFOBT, and associated pathology services obtained from audit of GP records, and data from the MBS, VAED and NBCSP records. Any other associated changes in health care utilisation will be captured through access to participants’ MBS and GP record data. Indirect costs will not be included.Five-year impact on risk-appropriate screening behaviour and health service utilisation will be measured but only utilising objective, administrative data. Impact on screening behaviour will be assessed as per the primary outcome.

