## Statistical methods

### Statistical methods for primary and secondary outcomes {20a}

The primary analysis will be based on the intention to treat principle where all randomised participants will be analysed in their allocated study arm. Baseline characteristics of the two arms will be summarised using descriptive statistics. Possible differential attrition will be assessed by comparing baseline characteristics of those who withdraw against those who remain in the study. For the primary outcome analysis, a generalised linear model with the identity link function and binomial family will be used to estimate the absolute difference in the proportion of participants who have had risk-appropriate CRC at 12 months between intervention and control arms. We will also estimate the odds ratio using logistic regression. In all regression analysis, the randomisation stratification factor, general practice, will be included as fixed effect. The absolute (between-arm difference in the proportions) and relative (odds ratio) estimated effect sizes will be presented with their respective 95% confidence interval (CI), and the *p*-value will be estimated using logistic regression. Comparisons between arms on continuous secondary endpoints will be undertaken using a linear mixed-effects model that includes arm (intervention and control), general practice and time (baseline, 1, 6 and 12 months) as fixed effects and individuals as random effect, with two-way interaction between arm and time, except baseline where study arm means will be constrained to be equal. Differences between arms on binary secondary endpoints will be estimated using logistic regression using generalised estimating equations with robust standard errors to allow for the repeated outcome measures on individuals (1, 6 and 12 months), adjusting for general practice. All analyses will be conducted in Stata 17 [54].

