Due to lengthy delays in approvals from Services Australia for the trial to include collection of MBS data from participants, the trial steering committee decided that recruitment should begin before this approval was granted. This resulted in the first study participants not providing written consent for the release of their MBS data at the time of recruitment. Approvals have now been granted from Services Australia and these initial participants are being recontacted for the purposes of this consent. However, this may result in some participants not being consented to access their MBS data (private colonoscopies and iFOBT kits ordered by GPs outside the NBCSP). The risk is that there may be screening events for some participants not captured in any other data source (GP records, VAED and NBCSP) which would alter the assessment of their primary outcome. However, in our experience of a previous trial using similar methods (paper in submission), there is sizeable overlap between information about colonoscopies and GP-ordered iFOBT captured in MBS, VAED and GP records. Therefore, we anticipate that the overall risk of bias in determining the primary outcome due to this issue is low.

This trial includes secondary outcomes that allow us to examine the effect of the intervention on behavioural predictors of CRC screening; this is particularly important should we not observe a clinically important difference in the proportion of risk-appropriate screening between arms. These secondary outcomes were selected from our pilot and development work of the intervention [39, 60], based on health behaviour theories [49, 61]. They include elements to determine whether participants’ attitudes towards screening were altered by the intervention, their perception of their own risk of CRC, the impact of risk prediction on their cancer worry and whether any non-adherence to screening recommendations can be attributed to GP behaviour rather than patient behaviour (e.g. if participants were not referred for discussion of colonoscopy or an iFOBT was not ordered by the GP, as determined by audit of GP records). These secondary outcomes will also provide valuable data to incorporate into a GP implementation strategy should the trial show a positive impact on risk-appropriate screening behaviour, allowing this strategy to focus on elements of the intervention that are proposed to have the greatest behavioural effect.

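### Screening intention is collected on five ordered levels but defined only as a proportion, which discards the grading; a prespecified full-scale analysis beside the proportion would be a cheap gain (minor).

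*Protocol article*

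**What the plan says.** Three parts of the protocol article together fix how intention is handled.

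- **Collection** (Plans for assessment and collection of outcomes {18a}, Secondary outcomes): intention to be screened, or to discuss screening with the GP, "will be measured with a five-point Likert scale from strongly disagree to strongly agree". Table 1 schedules it at enrolment as well as at follow-up.
- **Outcome definition** (Outcomes {12}, Secondary outcomes): "Proportions with CRC screening intentions at 1 and 6 months based on the Theory of Planned Behaviour". No cut-point is given.
- **Analysis** (Statistical methods {20a}): two families of model are named for secondary endpoints. One is for continuous measures: "Comparisons between arms on continuous secondary endpoints will be undertaken using a linear mixed-effects model", with baseline in the model and arm means constrained equal there. The other is for binary measures: "Differences between arms on binary secondary endpoints will be estimated using logistic regression using generalised estimating equations with robust standard errors", using the follow-up visits and adjusting for general practice. No ordinal model is named.

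The comparative risk item follows a similar path. It is collected "comparatively to an ‘average’ person, from 1 — much lower — to 7 — much higher" and summarised as "proportions estimating themselves as average, higher than average and lower than average at 1, 6 and 12 months".

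On the role of the behavioural secondary outcomes, the Discussion says "this is particularly important should we not observe a clinically important difference in the proportion of risk-appropriate screening between arms".

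**The concern.** A proportion can go only to the binary model. Once five levels are cut into two, a shift from agree to strongly agree, or from strongly disagree to neutral, is recorded as no effect. The binary route as stated also leaves out the baseline intention score, which the linear mixed model would use.

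The plan handles a similar format differently elsewhere. The Preventative Health Model items are also five-point agreement items, but they are summed and compared as means. No reason is given for the different choice for intention.

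For the comparative risk item, seven levels become three, and a three-level outcome does not enter a binary model without a further cut.

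What is at stake is interpretation. If the primary outcome shows no clinically important difference, the behavioural outcomes are meant to show whether attitudes moved. An insensitive summary of intention makes it easier to conclude wrongly that they did not. The sample size was set for the primary outcome, so there is no reserve of power planned for intention.

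**Working it through.** **1. The plan's own figure.** The documents state no power for intention, only for the primary outcome: 68% vs 51%, 80% power, two-sided 5%. The pooled-variance formula for two proportions, with mean proportion 0.595, is

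n = [1.96·√(2·0.595·0.405) + 0.842·√(0.68·0.32 + 0.51·0.49)]² / 0.17² = 129.7, so 130 per arm.

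130/0.95 = 136.8, so 137 per arm and 274 in total. The stated sample size reproduces. I take 130 per arm as the number analysed; loss of questionnaires is not given and could be larger.

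**2. Assumptions (none is in the documents).** One visit; cut at agree or above; a common odds ratio (OR) across the scale; and the control distributions below.

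**3. Formulas.**
- Full scale, proportional odds: power = Φ(√[n·(ln OR)²·(1 − Σm³)/6] − 1.96), where m is the mean of the two arms' probabilities at each level.
- Binary: power = Φ([d − 1.96·√(2p̄(1−p̄)/n)] / √[(p₁(1−p₁) + p₂(1−p₂))/n]).

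**4. Worked case.** Control 5/10/25/40/20% from strongly disagree to strongly agree, OR 2.0, n = 130.
- Agreement is 60%, odds 1.5. Doubled, the odds are 3, so 75% in the intervention arm.
- Intervention distribution: 2.6/5.5/16.9/41.7/33.3%, and Σm³ = 0.0968.
- Full scale: √(130·0.4805·0.9032/6) = 3.066, and Φ(3.066 − 1.96) = 86.6%. A Wilcoxon simulation gave 86.3%.
- Binary: p̄ = 0.675, and (0.15 − 1.96·0.0581)/0.0573 = 0.63, so 73.6%.
- Loss: 13.0 points. A comparison of mean 1–5 scores gives 84.3%.

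**5. Other control distributions, 130 per arm.** Power in %, full scale / binary, with the loss in points taken before rounding.

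| Control distribution (%) | Agree or above | OR 1.5 | OR 1.8 | OR 2.0 |
|---|---|---|---|---|
| 20/20/20/20/20 | 40% | 45.5 / 36.7 (8.9) | 76.3 / 65.3 (11.0) | 88.4 / 79.3 (9.0) |
| 10/20/40/20/10 | 30% | 44.1 / 33.9 (10.1) | 74.8 / 62.1 (12.7) | 87.3 / 76.8 (10.5) |
| 5/10/25/40/20 | 60% | 43.5 / 34.3 (9.2) | 73.9 / 60.2 (13.7) | 86.6 / 73.6 (13.0) |
| 2/3/10/45/40 | 85% | 40.6 / 18.9 (21.7) | 70.1 / 32.5 (37.6) | 83.3 / 41.2 (42.1) |
| 1/2/5/32/60 | 92% | 35.4 / 12.5 (23.0) | 62.0 / 20.1 (41.9) | 75.5 / 25.2 (50.3) |

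At 110 per arm the first three rows lose about 8 to 14 points and the last two about 19 to 46.

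**6. Wider assumptions, 130 per arm.** Adding OR 2.5 and a low-agreement distribution, the cut at agree or above loses 2.9 to 56.5 points. A cut at strongly agree only loses 1.2 to 58.5. Near the ceiling that second cut loses very little: 1.9 points in the last row at OR 2.0. The unstated cut-point therefore matters as much as the decision to dichotomise.

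**7. Case against the full scale.** Suppose the intervention only moves people from neutral to agree, taking agreement from 60% to 75% with nothing else changed. Binary power is then 73.6%, Wilcoxon 31.3% and mean score 20.8%. The order reverses.

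**The case against.** The proportion intending to be screened is a legitimate and readable estimand. It sits naturally beside a binary behavioural primary outcome, and the plan gives a suitable model for it. No power is claimed for intention. All of that stands, and it is why this is not an error.

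The common upward shift is itself doubtful here. The protocol expects 25% of the sample to be aged 45–49 and 90% of those to be at average risk, which is 0.25 × 0.90 = 22.5% of participants for whom no screening is the appropriate course. Their intention could reasonably fall. Proportional odds also favours a full-scale test by construction.

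The Preventative Health Model is a validated multi-item instrument with summed subscales, so a shared response format does not oblige the same summary. Its subscales and the Cancer Worry Scale are already compared as means, and perceived risk is also collected on a 0–100 scale and summarised as a mean. Explaining a null primary result does not rest on intention alone.

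Finally, the statistical analysis plan is not shown and may add a score or ordinal analysis. That is possible. However, what the protocol defers to it is additional analyses, adherence adjustment and missing data; the form of this outcome and its model are already set in the protocol.

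A reader might infer that the plan forfeits a definite amount of power, or that intention is the outcome that matters most after a null result. The documents support neither. They give no inputs from which a loss could be derived, and the Discussion passage speaks of the secondary outcomes as a group.

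**Conclusion.** The point holds as a minor efficiency weakness. Five ordered levels are reduced to a proportion with no stated cut-point, and the only model in the protocol that fits is binary, for one of a group of outcomes that the protocol calls particularly important if the primary result is null.

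The size is conditional throughout. It is roughly 9 to 14 points of power for central or moderately high agreement and up to about 50 near the ceiling, given a cut at agree or above, a common odds ratio of 1.5 to 2.0, one visit and about 130 per arm. Over wider assumptions it is about 1 to 58 points, and it becomes a gain if movement occurs only across the cut. Repeated visits would raise power for both approaches and were not modelled.

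Because the order can reverse, the evidence favours adding a full-scale analysis. It does not favour dropping the proportion or reducing it to description only.

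**What to change.** In Outcomes {12} and Statistical methods {20a}, before any unblinded analysis:

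- Keep the proportion with screening intention, and state the cut-point in advance.
- Add a prespecified between-arm analysis of each intention item on its full scale. The simplest choice is the linear mixed model already specified, applied to the 1–5 score; it also uses the baseline score collected under Table 1. The alternative is an ordinal (cumulative-logit) model with standard errors clustered on participant, with arm, visit, their interaction and general practice.
- Analyse the seven-point comparative risk item on its full scale in the same way, and report the three-category proportions beside it, since movement there may go in either direction.

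This needs no new data, visits or participants. The cost is one extra analysis per item, a check of proportional odds if the ordinal model is chosen, and an effect measure (mean difference or common odds ratio) that is less readable than a proportion. Keeping the proportion alongside covers that last cost.

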### Participant timeline {13}

Table 1 shows the participant timeline.

**Table 1 Tab1:** SCRIPT trial participant timeline

	Trial period						
	Enrolment	Allocation to intervention		Post-allocation^**a**^			
**Time point**	***0***	***0***	***2–3 weeks***	***1 month***	***6 months***	***12 months***	***5 years***
**Enrolment**							
**Eligibility screen**	X						
**Informed consent**	X						
**Allocation to intervention**		X					
**Interventions**							
***SCRIPT intervention***			X (PRS report)				
***Control***		X (cancer risk reduction brochure)				X (PRS report)	
**Assessments**							
***Demographics***	X						
***CRC screening + health service utilisation data (GP record, MBS, NBCSP, VAED)***						X	X
***CRC screening data (participant report)***	X			X	X	X	
***CRC risk perception***	X			X	X	X	
***Cancer-specific anxiety (Cancer Worry Scale)***	X			X	X	X	
***Influences of CRC screening behaviour (Preventative Health Model)***	X			X	X	X	
***Cancer screening intentions***	X			X	X	X	

^a^For the intervention arm, time points are after provision of PRS report and for the control arm, after standard cancer risk reduction information (i.e. last information regarding CRC risk and screening information)

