### Trial design {8}

The SCRIPT trial is a multi-site, phase II individually randomised controlled trial [26]. The study will test the implementation of the SCRIPT intervention in primary care, aiming to increase risk-appropriate CRC screening. Participants will be randomly allocated 1:1 to the intervention arm who will receive the SCRIPT intervention or the control arm who will receive standard cancer prevention information (Additional file 1).

In the intervention arm, personalised CRC risk results from the PRS and resulting screening recommendations will be available 2–3 weeks after sample provision, when the researcher will discuss the results with participants. Standard cancer prevention information will be discussed with control arm participants immediately after randomisation. All participants will be followed up via questionnaires at 1, 6 and 12 months and collection of objective data regarding their CRC screening behaviour from their medical records at 12 months. DNA will be collected from all participants at baseline, and the PRS result and screening recommendations will be offered to control participants after the primary endpoint (12 months). Given the nature of the intervention, it is not possible to blind participants to their allocation; however, researchers collecting follow-up data will be blinded.

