## Interventions

### Explanation for the choice of comparators {6b}

Control participants will have a standardised consultation in person or over the telephone, delivered by the second research assistant, during which an adapted version of the Cancer Council Victoria 2018 ‘Cut your cancer risk’ brochure will be discussed (Additional file 1), and a hard copy provided via post or email. The focus of the control consultation will be about how to reduce cancer risk by modifying behaviour, along with brief information about the three national cancer screening programs (biennial iFOBTs for bowel cancer from 50–74, biennial mammogram for breast cancer from 50–74 and cervical screening tests every 5 years from 25–74). This is designed as a credible ‘attention control’ while not altering ‘usual care’ since it is unlikely to prompt discussions about CRC risk or screening with their GP. It also increases engagement in the trial for control participants to minimise attrition.

The control arm will have the option to receive their DNA test results report after the 12-month intervention period from the time of recruitment. This strategy has been employed to increase engagement and participation in the trial. Control participants will be reminded of this option when told of their arm allocation and asked if they want to take this up at the end of the final questionnaire for the study, sent 12 months after recruitment. For those who would like their genomic test results, it will be discussed with them over the phone, a hard copy sent to them via post and a copy placed in their GP record.

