Results from the PRS test will be available approximately 2–3 weeks after their pre-test consultation and sample provision. Participants in the intervention arm will discuss the results of their PRS with the research assistant. They will be asked to make an appointment with their GP directly after the risk result appointment. As a first option, both result discussions will occur in person at the participant’s GP clinic. Given the current COVID-19 pandemic, in the case of lockdown rules preventing study staff from attending the clinic, results will be given using an online meeting tool (e.g. Zoom [41] or doxy.me [42]) with a screensharing facility, allowing for the researcher to show the participant their risk report, prior to posting them a paper copy.

At the meeting, a report summarising the participant’s CRC risk and screening recommendations will be given to them to discuss with their GP. Those who are due screening with an iFOBT will be encouraged to discuss with their GP and either provided an iFOBT kit on the day, or their GP will order one to be sent in the post via the National Cancer Screening Register. GPs will have the final responsibility to organise appropriate CRC screening.

Examples of risk reports can be seen in Figs. 1 and 2. The risk report is designed to increase response efficacy for screening (a person’s belief that the behaviour will reduce their disease risk). A version of the risk report tailored for the GP’s use will also be uploaded to the participant’s GP record (Additional files 2 and 3). All participants recommended an iFOBT from their PRS will be given a brief demonstration on its use via a standard NBCSP video to increase their self-efficacy to perform the test [43]. To encourage adherence with iFOBT, we will send a reminder to complete testing as an SMS message after 1 month to participants in the intervention arm who are due an iFOBT. For those who have reported having polyps found on previous colonoscopy, an information sheet regarding the NHMRC guidelines on surveillance colonoscopy after polypectomy will be given to participants’ GPs to assist their clinical discussion and determine the timing and need for further colonoscopic surveillance.

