## Data collection and management

### Plans for assessment and collection of outcomes {18a}

#### Primary outcome

The primary outcome is the proportion of participants who have had risk-appropriate CRC screening at 12 months’ follow-up. The appropriate type and frequency of screen will be determined by participant’s level of CRC risk as follows:

For those aged 50 years and over:*Average-risk category*: for participants whose 10-year absolute risk of colorectal cancer is less than 4% based on their PRS, family history, age and sex (intervention only) and who do not fall into the moderate risk category of the 2017 NHMRC-endorsed Australian guidelines [5] (both trial arms), iFOBT every 2 years is considered risk-appropriate screening.*Moderate-risk category*: for participants whose 10-year absolute risk of colorectal cancer is greater than or equal to 4% based on their PRS, family history, age and sex (intervention only), or they had a self-reported family history of CRC (both trial arms) that places then in the moderate risk category of the 2017 Australian guidelines [5], risk-appropriate screening is colonoscopy every 5 years.

For those aged under 50 years:*Average-risk category*: for participants whose 10-year absolute risk of colorectal cancer is less than 1% based on their PRS, family history, age and sex (intervention only) and do not fall into the moderate risk category of the 2017 NHMRC-endorsed Australian guidelines [25] (both trial arms), risk-appropriate screening is no screening until aged 50 years.*Moderate-risk category*: for participants whose 10-year absolute risk of colorectal cancer is greater than or equal to 1% based on their PRS, family history, age and sex (intervention only), or they had a self-reported family history of CRC (both trial arms) that placed then in the moderate risk category of the 2017 Australian guidelines [5], risk-appropriate screening is iFOBT every 2 years until aged 50 years.

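### Table 1 starts the 12-month clock at PRS report delivery in the intervention arm but essentially at randomisation in the control arm, so early screening in the intervention arm has no clear status

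*Protocol article*

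**What the plan says.** All references are to the Protocol article.

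- **Origin of the time points (Table 1, footnote a).** "For the intervention arm, time points are after provision of PRS report and for the control arm, after standard cancer risk reduction information". The footnote marker sits on the Post-allocation header. It therefore covers the 12-month column, where GP record, MBS, NBCSP and VAED data are collected.
- **Control arm (Trial design {8}).** "Standard cancer prevention information will be discussed with control arm participants immediately after randomisation".
- **Intervention arm (Intervention description {11a}).** "Results from the PRS test will be available approximately 2–3 weeks after their pre-test consultation and sample provision". Table 1 places the report at 2–3 weeks on a scale where allocation is time 0.
- **Non-attenders (section 11c).** "For those who do not attend their scheduled risk result appointment, three attempts will be made to reschedule". Then: "After three unsuccessful contacts or three non-attendances at their result appointment, they will be sent their risk results in the post". No maximum delay is given.
- **Withdrawal before results (section 11b).** "If this occurs prior to provision of CRC risk results, participants will not receive the full intervention". Section 18b adds that objective screening data are still collected after withdrawal from contact.
- **Primary outcome (section 18a).** "The primary outcome is the proportion of participants who have had risk-appropriate CRC screening at 12 months’ follow-up". No start date is given. The same section uses enrolment as the line between earlier screening and follow-up screening.
- **Analysis (section 20a).** Intention to treat, with all randomised participants in their allocated arm.

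**The concern.** An intention-to-treat comparison of a 12-month proportion needs one time origin, fixed at or before randomisation, in both arms. Footnote a gives the intervention arm an origin that happens after randomisation and depends on attendance. Three things follow.

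1. Screening after randomisation but before the report is not past screening under section 18a, and it falls before time zero under footnote a. The document does not say whether it counts. The control arm has no such gap.
2. A participant who withdraws before results has no report date, and so no window. That participant can still have objective data and belong to the analysis set.
3. The intervention window closes later, relative to randomisation, than the control window.

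The gap need not be quiet. Recruitment is tied to a GP appointment within about a week, and section 11c itself monitors GP-ordered iFOBTs in controls during the four weeks after consent. At stake is a small one-arm bias whose sign depends on an unstated counting rule.

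**Working it through.** **The plan's own figure.** Section 14 plans for 68% vs 51%, 80% power, two-sided 5%, and 5% missing. With pooled variance and no continuity correction, the mean proportion is 0.595:

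n = [1.960 × √(2 × 0.595 × 0.405) + 0.842 × √(0.68 × 0.32 + 0.51 × 0.49)]² / 0.17² = 130 per arm.

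130 / 0.95 gives 137 per arm, or 274 in total. The figure reproduces. It does not depend on where the window starts, so the 17-point target is a fair yardstick.

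**Window positions, in weeks from randomisation**

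| Arm | Opens (footnote a) | Closes |
|---|---|---|
| Control | about 0 | about 52 |
| Intervention, report on schedule | 2–3 | 54–55 |
| Intervention, non-attender | later, no limit stated | later |
| Intervention, withdrew before results | undefined | undefined |

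The nominal length is 12 months in both arms. Only the position relative to randomisation differs.

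**Size of the shift.** Inputs from section 14 are 12-month proportions of 40% (control) and 60% (intervention) at age 50 and over. The gap g is 2–3 weeks, from Table 1. Assumption: a constant hazard h = −ln(1 − p) / 52.18 per week, so h = 0.00979 at p = 0.40 and 0.01756 at p = 0.60. The share screened in the gap is G = 1 − exp(−h × g).

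- **(a) Gap events count and the window closes 12 months after the report.** The extra proportion is (1 − p) × G.
- **(b) Gap events are dropped and the window closes 12 months after the report.** The proportion counted is (1 − G) × p, so the loss is p × G. This assumes that a person screened in the gap is not screened again in the window.

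| p | g (weeks) | G | (a) gain, points | (b) loss, points |
|---|---|---|---|---|
| 0.40 | 2 | 0.0194 | 0.6 × 0.0194 = +1.2 | 0.4 × 0.0194 = −0.8 |
| 0.40 | 3 | 0.0289 | 0.6 × 0.0289 = +1.7 | 0.4 × 0.0289 = −1.2 |
| 0.60 | 2 | 0.0345 | 0.4 × 0.0345 = +1.4 | 0.6 × 0.0345 = −2.1 |
| 0.60 | 3 | 0.0513 | 0.4 × 0.0513 = +2.1 | 0.6 × 0.0513 = −3.1 |

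Section 14 expects 25% of the sample to be aged 45–49. With no shift in that group, the whole-arm effect is 0.75 times the table: +0.9 to +1.5 points under (a) and −0.6 to −2.3 points under (b). For average-risk participants under 50, appropriate means no screening, so a longer window works the other way. The effect there is small, because the plan assumes that 95% of them are appropriately unscreened at 12 months.

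**The case against.** The best defence has four parts.

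- **The footnote sits in a visit schedule.** The cross in the 12-month column may mark when records are pulled, not how events are windowed, and exact date windows are commonly left to the SAP, which is not shown. This stands in part: the SAP may settle it. But the protocol does more than leave a gap. It states an origin that differs by arm, and neither section 12 nor section 18a overrides it.
- **Delivery anchoring has a rationale.** It gives both arms a nominal 12 months after their last risk information. That is sensible for questionnaires on worry and risk perception. For a dated event under intention to treat, it trades away the common origin.
- **Some edge cases are covered.** Non-attenders are posted their results and so have a date. Only those who withdraw before results have none.
- **The effect is small.** This stands.

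Three stronger readings are tempting, and the document does not support them.

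- **Self-contradiction with section 6b.** A reader might set the footnote against the wording that controls are "asked if they want to take this up at the end of the final questionnaire for the study, sent 12 months after recruitment". That passage concerns controls only. Their information is given at randomisation, so the two clocks agree. The tension is with the enrolment boundary in section 18a.
- **Due dates.** A reader might infer that the later close lets more intervention participants fall due. The eligibility examples for those over 50 match the scoring intervals: iFOBT not within 1 year on a 2-year cycle, colonoscopy not within 3 years with iFOBT due after 4, and colonoscopy not within 4 years on a 5-year cycle. All are due by month 12 already.
- **Larger losses.** A reader might take the whole of G, 1.9 to 2.9 points at the 40% rate, as the loss. That needs a window opening at the report and closing 12 months after randomisation. The footnote's window closes 12 months after the report, so later events offset part of the loss.

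**Conclusion.** The point holds as a definitional flaw in the primary outcome window. The origin differs by arm, it is a post-randomisation event in one arm, and it is undefined for anyone who withdraws before results. Screening between randomisation and the report is left without a clear status in the intervention arm alone.

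For a 2–3 week gap, the shift in those aged 50 or older lies between about −3 and +2 points, against a planned 17. It is unlikely to decide the result by itself. The estimate rests on a constant hazard, on the plan's 40% and 60% rates, and on the report arriving on schedule. Longer delays would enlarge it for the participants concerned, and the document gives no figure for how many or how long. The sign cannot be stated until the counting rule is fixed.

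**What to change.** For the primary outcome, state in section 18a and the SAP that the window runs from the date of randomisation to 12 months after it in both arms, and that every dated objective screening event inside it counts, whether or not the PRS report has been given. Where self-report is used because no objective data exist, apply the same dates.

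Limit footnote a to the questionnaires, where delivery-based timing can stay, and align it with the enrolment boundary in section 18a. Keep the report-anchored window as a sensitivity analysis, with a stated rule for events in the gap and for participants who never received a report.

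The cost is wording. GP record, MBS, VAED and NBCSP events are dated and can be re-windowed, and the sample size of 274 is unchanged. The one real downside is that intervention participants have about 2–3 fewer weeks after their report inside the window. The sensitivity analysis will show whether that matters. Settle it before the blinded data review.
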